### ***Interim analysis***

An interim analysis for efficacy, safety and trial quality indices is planned at the midpoint of patient enrolment (approximately 45 patients per group). There is no plan to stop the trial prematurely for efficacy or futility based on the primary or secondary trial endpoints. Data at the time of the interim analysis will be presented to the Data Safety and Monitoring Board (DSMB) for review, who may advise that the trial continue without

modification, continue with changes to the protocol, or be discontinued prematurely.

With respect to the statistical interpretation of safety data, the DSMB may recommend termination or modification of the trial if mortality rates exceed statistical thresholds as described in Appendix 1. However, we do not propose that the DSMB be strictly bound by pre-specified criteria, because of the complexity of the trade-offs between safety, efficacy, and the possibility that new information will change considerations. Rather, consideration of stopping guidelines requires a reasoned judgment based on all information that is available at the time of data review.

## **9.2 Number of subjects planned to be enrolled**

We will enrol 180 patients (approximately 90 in each treatment arm).

Based on a recent clinical trial of L-arginine as adjunctive treatment for severe malaria, among patients who subsequently recovered, Ang-2 decreased by 2700pg/mL/day (95%CI 1800-3600pg/mL/day)[33]. We assume that a 50% change in this parameter would represent a clinically significant therapeutic effect. By standard calculations for normally distributed data, 80 patients per group will provide 80% power to detect a difference between two treatment arms of 1350pg/mL/day at  $p=0.05$  (two-sided). This corresponds to a 50% difference in the rate of change of Ang-2 between the arms. To account for possible dropout, loss to follow-up, and/or non-evaluable data of 10% of patients, approximately 90 patients per study arm are required.

However, these calculations do not reflect the analytic plan. Therefore, a simulation study was performed. A number of assumptions needed to be made, such as within patient correlation and Ang-2 variability. Patient Ang-2 data were simulated using a

multivariate normal distribution. A simple autoregressive correlation structure was used with correlations of 0.75, 0.5 and 0.25 for lags 1, 2 and 3 respectively. In previous studies, variability appears proportional to the mean[33]. Simulations were run with three different relationships where the standard deviation was taken to be 40%, 50% and 80% of the Ang-2 mean at each time point. Both groups were assumed to start at Ang-2 levels of 15,000 pg/mL and the average values at each of days 1, 2 and 3 based on the hypothesized slopes of Ang-2. One thousand replications were performed at each standard deviation relationship and treatment effect. The mixed effects models were fit and the likelihood ratio test was used to test the hypothesis of no time by treatment interaction at the 5% level (two tailed). Table 4 shows the results of the power simulations.

Table 4: Power simulations for 90 patients per group

| Standard Deviation
(% of mean) | Slope Difference               |                                        |                                        |
|-------------------------------------------|---------------------------------------|----------------------------------------|----------------------------------------|
|                                           | 30% change
(810 pg/mL/day) | 40% change
(1080 pg/mL/day) | 50% change
(1350 pg/mL/day) |
| 40                                        | 82%                                   | 97%                                    | 99%                                    |
| 50                                        | 66%                                   | 89%                                    | 98%                                    |
| 80                                        | 42%                                   | 60%                                    | 80%                                    |

Estimates from the Jinja Regional Hospital indicate that a minimum of 175 patients with moderately severe and severe malaria (excluding patients with SMA) are admitted annually. This implies that accrual of all patients to meet the required sample size will take approximately 12-18 months (180 patients with severe malaria).

At the interim analysis (midpoint of enrolment), we may perform a sample size re-calculation using the observed variance estimates, the observed means at each time in the placebo group, and the observed dropout rate (*a priori* estimate: 10%). Sample size may be increased if feasible and if suggested by this analysis at midpoint of enrolment.

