## **3 TRIAL OBJECTIVES**

The objective of this trial is to determine the efficacy of inhaled nitric oxide (iNO) for the adjunctive treatment of *P. falciparum* malaria.

Our specific aims are:

1. To determine whether supplemental iNO gas (80 ppm) in addition to Ugandan Standard of Care treatment accelerates the rate of decline in angiopoietin-2 from admission levels in children with severe malaria compared to Standard of Care treatment plus placebo.
2. To determine the clinical efficacy of iNO in severe malaria.
3. To determine the tolerability and safety of iNO in severe malaria.

The working hypothesis is that young children hospitalized with malaria will benefit from adjunctive iNO in addition to standard therapy, as determined by more rapid improvement in serum angiopoietin-2 (Ang-2) levels (an objective and quantitative biomarker of malaria disease severity) as well as other clinically relevant outcomes. We will test this hypothesis by comparing the daily rate of change of Ang-2 over the hospital admission (primary outcome) between the two groups randomized to receive iNO or placebo (room air). We will also compare relevant clinical outcomes including efficacy, safety and tolerability (secondary outcomes).

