***Primary outcome***

The daily change in Ang-2 over the hospital admission will be the primary efficacy outcome. Elevated Ang-2 levels are associated with poor clinical outcome in severe malaria[33, 34] and Ang-2 has been used to follow disease progression and recovery in previous studies of malaria[33]. Thus, Ang-2 is an objective, quantitative marker of disease severity, validated for longitudinal follow-up of patients with malaria. Ang-2 levels will be measured longitudinally at admission (day 0), day 1, day 2 and day 3 of hospital admission. In patients treated for severe malaria who survive the infection, Ang-2 levels have been shown to decrease linearly during recovery at a mean rate of 2700pg/mL per 24h[33].

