***Serious Adverse Event or Serious Adverse Drug Reaction***

*A serious adverse event (experience) or reaction is any untoward medical occurrence that at any dose:*

- *results in death,*
- *is life-threatening,*
- *requires prolongation of existing hospitalisation, or*
- *results in persistent or significant disability/incapacity*

In this trial of critically ill children hospitalized with severe malaria, mortality is expected to occur in approximately 20% of participants who receive standard medical care[90].

Monitoring serious adverse events during the trial is therefore complicated by the fact that death is part of the natural progression of disease, even under conditions of optimal clinical care (Uganda standard of care). We propose to monitor mortality continuously to detect variations above the baseline expected mortality rate, to allow for early implementation of corrective actions, if required.

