## **9.7 Selection of subjects to be included in analyses**

All randomized subjects will be included in the primary *intention-to-treat* analysis (change of Ang-2 over time). A secondary *per-protocol* analysis may be performed

including only patients with evaluable data who received the study gas for the proscribed duration (72 hours).

HIV co-infection, co-existent bacteremia and/or meningitis, and blood transfusion may affect Ang-2 levels and may represent effect modifiers of iNO treatment. We expect that randomization and blinding will ensure relatively even distribution of these co-variables between treatment and control groups, although these co-variables may add unexplained variance (random error) in the dependent variable (Ang-2). We will therefore conduct a subgroup analysis of iNO effect among HIV negative patients without bacteremia who do not undergo blood transfusion, to examine the role of iNO in this carefully selected patient population. Additional subgroup analyses will be conducted according to other possibly important co-variables: age < 5 years or ≥5 years; cerebral malaria or other severe malaria syndrome (respiratory distress); HIV seropositivity; and severe anemia.

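### Section 9.2 takes its Ang-2 slope from recovered patients and Table 4 describes no deaths or losses, so the stated power is optimistic, mainly in the SD 80% row

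*Protocol*

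**What the plan says.** Section 9.2 takes its reference rate from patients who got better: "among patients who subsequently recovered, Ang-2 decreased by 2700pg/mL/day (95%CI 1800-3600pg/mL/day)[33]. We assume that a 50% change in this parameter would represent" a worthwhile effect. Half of 2,700 gives the target of 1,350 pg/mL/day, which 9.2 also describes as a 50% difference between the arms in the rate of change. The primary-outcome text in 4.1 (repeated in 7.1) restricts the rate in the same way: "In patients treated for severe malaria who survive the infection, Ang-2 levels have been shown to decrease linearly during recovery at a mean rate of" 2,700 pg/mL per 24 h.

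The analysed population is wider. Section 9.7 says "All randomized subjects will be included in the primary" intention-to-treat analysis. Section 8.1 says "mortality is expected to occur in approximately 20% of participants who receive standard medical care". Appendix 1 gives 6-29% in earlier trials, with a median of 19%, and plans on about 20%. Section 9.5 lists death before sampling is complete among the causes of missing Ang-2 data.

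The only allowance for loss is this: "To account for possible dropout, loss to follow-up, and/or non-evaluable data of 10% of patients, approximately 90 patients per study arm are required". Table 4 is headed as 90 patients per group. The simulation text gives baseline, correlations, SDs and slopes, but no deaths, dropout or missing samples.

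**The concern.** The slope describes patients who recovered, while the trial will analyse all randomised children, including those who die. Nothing in 9.2 connects the two groups. Two things can go wrong.

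- **Lost information.** Children who die early give few samples, and the 10% allowance for loss is not applied in Table 4.
- **A different mean slope.** If children who die have a flatter Ang-2 course, the control rate in all randomised children is below 2,700. A 50% effect is then smaller than 1,350 pg/mL/day.

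At stake is how a null result is read. If the true power for a 50% acceleration is 60-75% rather than 80%, a negative trial is weaker evidence against that effect than 9.2 suggests.

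**Working it through.** **Inputs from 9.2 and 9.1.** Baseline 15,000 pg/mL in both arms; correlations 0.75, 0.5 and 0.25 at lags 1 to 3; SD 40%, 50% or 80% of the mean; control slope 2,700; 90 per arm; day categorical; likelihood ratio test of time by treatment at two-sided 5%. Expected mortality is 20% (8.1, Appendix 1).

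**Inputs that are assumptions.** The Ang-2 slope of children who die; that half of them give a baseline sample only; that simulated negative values are set to 0; and a random-intercept model.

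**1. Reproduce the plan.** The enrolment figure follows: 80 / (1 - 0.10) = 89, stated as about 90. With negatives set to 0, simulation reproduces all nine cells of Table 4 within 2 points. The 50% column comes out at 100/98/79% against the stated 99/98/80% (SD 40/50/80%). Without that step the 80% row is about 35/51/68%. Another run of the 50% column gave 77% at SD 80%, so a few points of any gap in that row come from the simulation set-up.

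**2. Apply the plan's own 10% allowance.** 90 x 0.9 = 81 per arm.

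**3. Add 20% deaths with truncated sampling.** Survivors keep 2,700 against 4,050 (2,700 x 1.5). Children who die either decline like the others while observed, or stay flat.

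**4. Read 50% as half of the all-randomised control rate.** With zero decline in 20%, the control rate is 0.8 x 2,700 = 2,160 and the effect is 0.5 x 2,160 = 1,080 pg/mL/day. That difference is already a Table 4 column.

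**5. Keep 1,350 as an absolute difference,** with control at 2,160 and complete data.

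| Scenario | SD 40% | SD 50% | SD 80% |
|---|---|---|---|
| Table 4, 50% effect, as stated | 99% | 98% | 80% |
| Reproduced | 100% | 98% | 79% |
| 81 per arm (step 2) | 100% | 96% | 75% |
| 20% die, slope like the others (step 3) | about 100% | about 97% | 71-75% |
| 20% die, no decline (step 3) | about 98% | about 91% | 62-70% |
| 50% of 2,160, Table 4's 1,080 column (step 4) | 97% | 89% | 60% |
| Absolute 1,350, complete data (step 5) | 100% | 97% | 79% |

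Simulating step 4 directly gives 97/87/60%. The step 3 ranges come from separate runs and shift by some points with how long the remaining children who die are sampled, so they are indicative.

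**6. Vary mortality on the step 4 reading.** At 6% the control rate is 0.94 x 2,700 = 2,538; the nearest simulated rate, 2,565, gives about 100/96/75%. At 29% it is 0.71 x 2,700 = 1,917; the nearest, 1,890, gives 91/77/47%.

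**The case against.** The strongest reply is that 9.2 powers a stated difference of 1,350 pg/mL/day, and every Table 4 column carries an absolute figure. That stands for complete data: lowering the control rate alone barely changes power (step 5). It does not settle the point. Section 9.2 defines the target as half of the survivors' rate and equates 1,350 with a 50% difference between arms. Against 2,160, 1,350 would be 62.5% (1,350 / 2,160). Nor does it answer the loss of samples.

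It is also fair that the 1,080 column is already printed, that the quoted interval of 1,800-3,600 includes 2,160, and that 9.2 allows a midpoint recalculation from observed placebo means, variance and dropout. But the column is labelled a 40% change, and the recalculation is optional.

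Four stronger readings are tempting but not supported:

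- **Children who die certainly have a flatter slope.** Section 4.1 links raised levels to poor outcome. It gives no rate of change for non-survivors.
- **Only 72 per arm count (90 x 0.8), below the 80 required.** Section 9.5 has the mixed model use every available sample, so children who die still contribute.
- **Power falls to 61-76%.** That comes from the simple formula with an SD of 3,048 pg/mL/day solved backwards from 80 per group. The protocol states no such SD and says the simple calculation does not reflect its analysis.
- **The source patients received L-arginine, so a placebo slope would be lower still.** Section 9.2 says "Based on a recent clinical trial of L-arginine as adjunctive treatment for severe malaria" but not what the patients behind the 2,700 figure were given.

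**Conclusion.** The point holds in a limited form. Section 9.2 applies a recovered-patients' slope to an all-randomised analysis and shows power for 90 complete patients per arm, although the protocol expects about 20% deaths and names death as a cause of missing samples.

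The consequence is concentrated in the SD 80% row. The stated 80% becomes about 71-75% if children who die decline like the others, about 62-70% if they do not decline, and 60% if the effect is half of a control rate of 2,160. At SD 40% and 50% power stays above 80% in these scenarios. On the last reading it would drop below 80% at SD 50% only near the upper end of the mortality range.

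The size rests on an unknown slope in children who die and on when they die. It shrinks if most deaths come after day 3 in children whose Ang-2 was already falling. It is therefore right to call the stated power optimistic, but not to put one figure on the shortfall.

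**What to change.** In 9.2:

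1. State whether 1,350 pg/mL/day is an absolute target in all randomised children or 50% of their control rate. If it is the latter, give the assumed control rate.
2. Rerun Table 4 with the expected deaths (20%, range 6-29%), sampling cut short at death, and the 10% dropout. Use at least two assumed slopes for children who die, for example the same as survivors and no decline, and label them as assumptions.
3. Report the power for a 50% effect as the resulting range.

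The cost is one simulation rerun, a wording change and a less favourable stated power. Enrolment, procedures and the primary analysis do not change.

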#### **2.4 Justification of route of administration, dosage, dosage regimen, and treatment period**

iNO is US FDA-approved for the treatment of hypoxic respiratory failure in term and near-term neonates at a dose of 10-80ppm. We plan to use the upper range of the approved clinical dose to maximize the opportunity to observe a treatment effect, with appropriate monitoring for dose-dependent adverse effects (e.g., methemoglobinemia). iNO, a gaseous molecule, is administered by inhalational route. This route is attractive because of ease of delivery in resource-constrained settings, where IV drug delivery may be challenging. The 72 hour timeframe is based on the period during which iNO will produce the highest likelihood of benefit, since mortality, Ang-2 levels, and endothelial dysregulation are most pronounced in the first few days after admission. Ang-2 levels are elevated at presentation and return to normal levels in survivors over a period of approximately 72 hours[33].

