### **9.5 Procedure for accounting for missing, unused, and spurious data**

**Primary endpoint.** The primary endpoint of this trial involves collection of four serial (daily) venous blood samples for the measurement of rate of change of Ang-2. Missing data may therefore arise for a number of reasons including: premature discontinuation of study gas (not tolerated, safety issues, caregiver or health provider discretion); mortality event prior to complete collection of samples; or patient dropout. Our primary analysis using a mixed-effects linear model takes into account all available data points, and is able to handle missing data.

**Secondary endpoints.** Mortality at 48 hours is expected to be captured relatively completely, whereas 14-day mortality may be subject to loss to follow-up. Patients with missing data will not be included in computation of mortality, and we will report the number of missing cases. In the event that a significant mortality benefit is observed, we will perform a sensitivity analysis wherein patients with missing data are assigned an outcome of death (iNO group) or alive (placebo group), in order to systematically bias results toward the placebo group. If significant differences remain in this analysis, the result will be considered robust to adjustment for missing data. Our alternative analysis using Kaplan-Meier survival curves will censor patients at the point of last contact, in the case of missing data.

For the time to recovery endpoints, missing data will be handled by censoring patients at the time of the last documented time point. For other continuous variables, missing cases will be excluded from the analysis (two-way repeated-measures ANOVA), or will not affect the analysis (mixed-effects linear model).

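### Table 4 reports power for 90 complete children per arm: neither the 10% loss allowance nor deaths before day 3 have been deducted

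*Protocol*

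**What the plan says.** Protocol section 9.2 starts with a closed-form calculation: "80 patients per group will provide 80% power to detect a difference between two treatment arms of 1350pg/mL/day". It then enlarges the arms: "To account for possible dropout, loss to follow-up, and/or non-evaluable data of 10% of patients, approximately 90 patients per study arm are required". The same section says this calculation does not match the planned analysis and turns to a simulation of the mixed model, with a likelihood ratio test of the "hypothesis of no time by treatment interaction at the 5% level (two tailed"). The results appear under "Table 4: Power simulations for 90 patients per group". The listed simulation assumptions are the correlations, the SD as a share of the mean, the baseline mean and the slopes. No assumption about missing samples, dropout or death is listed.

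Elsewhere the protocol bears on how many children will give all four samples (days 0, 1, 2 and 3):

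- Section 8.1: "mortality is expected to occur in approximately 20% of participants who receive standard medical care". Section 4.9 and Appendix 1 use the same figure. None gives a time window.
- Section 2.4 justifies the 72-hour treatment period "since mortality, Ang-2 levels, and endothelial dysregulation are most pronounced in the first few days after admission".
- Section 9.5 lists, among the causes of missing Ang-2, a "mortality event prior to complete collection of samples". It also says the mixed model uses every available sample.

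**The concern.** The enrolled number has been simulated as if it were the analysable number. The step from 80 to 90 buys a margin against loss; the simulation then spends that margin as data.

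The allowance also leaves deaths unclear. If the 10% excludes them, a source of missing Ang-2 that section 9.5 recognises is not provided for. If it includes them, deaths alone use it up once half of the expected 20% fall before day 3, leaving nothing for withdrawals or unusable samples. The reference slope has the same complete-follow-up character: "among patients who subsequently recovered, Ang-2 decreased by 2700pg/mL/day (95%CI 1800-3600pg/mL/day").

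Table 4 is the power statement offered as matching the analysis. If it describes a trial in which no child dies, withdraws or loses a sample, a null result on Ang-2 would be read with somewhat more confidence than the design supports.

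**Working it through.** **Inputs (section 9.2 unless noted).** 90 per arm; baseline mean 15,000 pg/mL in both arms; decline 2,700 pg/mL/day, with slope differences of 810, 1,080 and 1,350 (30%, 40%, 50%); correlations 0.75, 0.5 and 0.25 at lags 1 to 3; SD 40%, 50% or 80% of the mean at each time; 5% two-sided. Section 9.1 treats day as categorical, so the interaction test has 3 degrees of freedom.

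**Step 1: the inflation.** 80 / (1 - 0.10) = 88.9, or 89 per arm. The stated figure of about 90 reproduces.

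**Step 2: reproduce Table 4 with no loss.** Multivariate normal data were simulated with control means 15,000 - 2,700t and iNO means 15,000 - (2,700 + d)t, where d is the slope difference. A random-intercept maximum-likelihood model was fitted and the interaction tested by a 3-df likelihood ratio test. With 90 complete children per arm, negative values set to zero and 10,000 replicates, all nine cells agree with print to within 2 points (second and third columns of the table below).

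Setting negative values to zero is an assumption; the protocol does not state it. It matters for the SD 80% row, where the chance of a negative value is Φ(-1/0.8) = Φ(-1.25), about 11%, against about 2% at SD 50% and under 1% at SD 40%. Without it the SD 40% and 50% rows still agree to about 2 points, but the SD 80% row gives 34/51/69 against the printed 42/60/80.

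**Step 3: remove children entirely.** 90 × 0.9 = 81 and 90 × 0.8 = 72 complete children per arm, same model.

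| SD / slope change | Printed | 90 complete | 81 (10% loss) | 72 (20% loss) |
|---|---|---|---|---|
| 40% / 30% | 82 | 83 | 79 | 75 |
| 40% / 40% | 97 | 97 | 96 | 93 |
| 40% / 50% | 99 | 100 | 99 | 99 |
| 50% / 30% | 66 | 67 | 62 | 58 |
| 50% / 40% | 89 | 89 | 85 | 81 |
| 50% / 50% | 98 | 98 | 96 | 94 |
| 80% / 30% | 42 | 40 | 37 | 34 |
| 80% / 40% | 60 | 61 | 57 | 52 |
| 80% / 50% | 80 | 79 | 76 | 70 |

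The fall is about 0 to 5 points at 10% loss and 0 to 10 at 20%.

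**Step 4: keep the samples taken before death.** The protocol gives no death times, so timing is assumed. Suppose 20% die, and of these half leave only the day-0 sample, a quarter leave two samples and a quarter three. With negatives set to zero and 1,000 replicates per cell (Monte Carlo error up to about 1.6 points), the 50% change column moves as follows:

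| SD | Complete | 20% deaths | 20% deaths + 10% other loss |
|---|---|---|---|
| 40% | 99.8 | 99.4 | 99.3 |
| 50% | 96.9 | 96.5 | 93.2 |
| 80% | 80.0 | 73.9 | 70.4 |

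Over all nine cells the fall is about 0 to 9 points with deaths alone and about 0.5 to 13 with both. With the same death timing but negatives left in (2,000 replicates), SD 40%, 30% change gives 77%, or 75% if all these deaths come before day 1.

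**Step 5: combined loss under two timings.** 20% deaths and then 10% other loss is 1 - 0.8 × 0.9 = 28%. Without setting negatives to zero (2,000 replicates), SD 50%, 30% change goes from 66.3% with complete data to 57.0% if losses are spread over days 1 to 3, and to 53.4% if all come before day 1. That fall of 12.9 points is the largest in this run.

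**Step 6: closed-form check.** 80 per arm at 80% power implies a slope SD of 1,350 × √(80/2) / (1.960 + 0.842), about 3,048 pg/mL/day. With 90 enrolled, power is 80.5% at 10% loss, 75.7% at 20% and 71.3% at 28%.

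**The case against.** The strongest reply is that the two percentages measure different things. The 10% covers children who leave or whose samples cannot be used. The 20% is overall mortality, used to set safety thresholds, with no time window. Deaths after day 3 cost no Ang-2 sample, and deaths between samples leave partial profiles that the mixed model keeps. This stands. A reader might infer that the 10% contradicts the 20% and cannot be right; the documents do not show that, because they never say how many deaths fall before day 3.

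A reader might also infer a general overstatement of 15 points. That figure appears only if the SD 80%, 50% change cell is scaled by 0.72 as though every lost child contributed nothing (80% to about 64.5%). No simulated scenario fell that far below its own complete-data result. Comparing the printed SD 80% row with a simulation that leaves negative values in would likewise mix attrition with a failure to reproduce the row.

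Finally, section 9.2 allows a midpoint re-calculation from the observed dropout rate, variances and placebo means, and section 5.3(c) allows one if discontinuation or withdrawal exceeds 10%. This is a real safeguard and, because it uses observed values, changing its 10% prior would add nothing. It is optional, however; section 5.3(c) does not name death; and neither provision corrects the power printed now.

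**Conclusion.** The point holds in a limited form. Table 4 is complete-data power at 90 per arm, so it omits the protocol's own 10% loss, and the 10% does not name deaths before day 3. The first part does not depend on when deaths occur.

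The effect is modest and uneven. At 20% deaths, SD 80% with 50% change falls from 80% to about 70-74%, SD 40% with 30% change from 82% to about 75-77%, and SD 50% with 30% change from 66% to about 58%. SD 40% with 50% change stays at about 99%. The lower end of each range treats these children as lost entirely or before day 1; fewer or later deaths before day 3 would cost less.

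These figures assume that loss is unrelated to Ang-2 and equal in both arms. Death related to Ang-2 could also bias the comparison; that was not computed. The SD 80% figures further depend on setting negative simulated values to zero. This is a correction to a stated power, worth making because it is cheap; it does not show that the trial is too small.

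**What to change.** In section 9.2:

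1. Re-run Table 4 for 90 randomised per arm with a stated share of deaths before each sample (for example 10% and 20% in total) plus 10% other loss, and print those figures as the trial's power. Failing that, label the present table as power with complete data.
2. State expected attrition for Ang-2 as early deaths plus other loss, and say whether the 10% includes deaths.
3. State how negative simulated values were handled, since the SD 80% row depends on it.

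The cost is a re-run of an existing simulation and a few sentences; the stated power becomes somewhat less favourable. No change to N, to the analysis or to conduct is needed.
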